**6. STUDY Design**

The study is a two-arm researcher-blind, randomised controlled trial (RCT), to test the effectiveness of the PFL home visiting programme and group Triple P for pregnant women from socioeconomically disadvantaged communities. The trial will involve 300 families in total. 200 will be randomly allocated into one of two groups:

(1) **High treatment group**, who will receive the PFL intervention (described below) (n=100)

(2) **Low treatment group** (n=100)

A third external comparison group will also be recruited from another similar community

(3) **External comparison group** (n=100).

**7. Trial Intervention**

**7.1 High treatment intervention**

*PFL* is a community-based home visiting programme (HVP) which aims to improve children’s school readiness skills by intervening during pregnancy and working with families until the children start school at age 4/5 years. The high treatment group will receive twice monthly home visits, lasting approximately one hour, delivered by mentors from a cross-section of professional backgrounds such as psychologists and family support specialists. Mentors will receive extensive training prior to programme implementation and monthly supervision thereafter to ensure fidelity to the programme model. Each family will be assigned the same mentor over the course of the intervention where possible. The mentors will use role modelling, demonstration, coaching, discussion, encouragement, and feedback to deliver the intervention, as well as direct interactions with the child in the presence of the parent. The aim of the visits are to support and educate the parents on key child rearing issues including the identification of developmental milestones and appropriate parenting practices that promote the children’s health, and cognitive and non-cognitive development. Each visit will be guided by a set of *PFL* ‘Tip Sheets’ which are based on pre-existing governmental and local non-governmental organisations’ recommendations, and present best-practice information on pregnancy, parenting, and child health and development. There are three sets of age-specific Tip Sheets - pre-birth-12 months, 1-2 years, and 2-4 years. There are approximately 150 *PFL* Tip Sheets as part of the programme’s curriculum. The mentors will be able to choose when to deliver the Tip Sheets within these specific time periods based on the age of the child and the needs of the family. The Tip Sheets will be given to the participants at the end of each visit to keep as an on-going resource.

The high treatment group will also be invited to participate in an additional parenting course (Triple P Positive Parenting Program; Sanders et al., 2003) when their children are between 2 and 3 years old i.e., after they have completed the 24-month assessment. Triple P promotes healthy parenting practices and positive parent-child attachment. The intervention will involve the delivery of Group Triple P which consists of 5 two-hour group discussion sessions and 3 individual phone calls facilitated by the mentors.

**7.2 Low treatment intervention**

Both the high and low treatment groups will receive some common supports including developmental materials and book packs. The developmental packs will consist of materials such as a baby gym, food utensils, safety items and an assortment of developmental toys. Both groups will also be encouraged by letter and text message to attend public health workshops on stress management and healthy eating which are already taking place in the community. The low treatment group will also have access to a support worker who can help them avail of community services if needed, while this function will be provided by the mentors for the high treatment group.

**7.3 External comparison group intervention**

The external comparison group, which will be selected from a socio-demographically similar community, will receive care-as-usual only. Care as usual, which is available to all pregnant women and infants in Ireland, is as follows: Expectant mothers are provided with an initial family doctor (G.P.)/obstetrician appointment at 12 weeks and a further 5 examinations for first time mothers and 6 for subsequent pregnancies. Antenatal classes are provided by local public maternity hospitals free of charge. Following birth, a G.P. examination is carried out for the baby at 2 weeks and mother and baby at 6 weeks. The mother is entitled to free in-patient, out-patient and accident and emergency/casualty services in public hospitals in respect of the pregnancy and the birth and is not liable for any hospital charges. In addition, checks by a public health nurse are generally carried out in the home in the weeks after birth and when the infant is 9, 18, and 24 months, but they are not mandatory. A schedule of immunizations in provided free of charge at birth, 2, 4, 6, 12, and 13 months

**8. Flow Chart**

**9. STUDY POPULATION**

All pregnant women from the PFL catchment communities (defined by the Northside Partnership who will manage the intervention) are eligible to participate.

**9.1 Eligibility criteria**

**Inclusion criteria**

1. Women (age 16+) pregnant between 2008 and 2010
2. Residing in the PFL catchment area
3. Willing to be assigned to either of the study intervention groups
4. Written informed parental/carer consent

**Exclusion criteria**

1. Under the age of 16
2. Not pregnant
3. Not residing in the PFL catchment area
4. No written consent provided.

**10. study Procedures**

**10.1 Recruitment**

Recruitment into the study will occur through one of two sources: 1) in the maternity hospital at the first booking visit or 2) self-referrals in the community. The recruitment process will involve substantial interactions and collaboration with the maternity hospitals in order to identify eligible women in a confidential manner. The hospital administrative staff will send the UCD evaluation team a weekly list stating the number of women from the *PFL* catchment area who are scheduled to have their first booking visit at the hospital the following week. The list will include the time and date of the visit, but for confidentiality reasons, no names or contact information will be included. The hospital staff will also flag the files of any eligible women on their computer system. By doing this, an alert will appear on the computer screen when the eligible women are booked into the clinic in the Outpatient Department (OPD). When this alert appears, the OPD staff will give the eligible women a *PFL* flier describing the programme and introduce them to the *PFL* recruiter who will be present in the waiting room of the clinic. The recruiter will then briefly explain the programme to the eligible participants and ask for their contact details. If the eligible participant is interested in learning more about the programme, the recruiter will take their contact details. Next, the recruiter will ring the potential participant later that day to set up a recruitment appointment to take place in the village centre or the family home. During the recruitment appointment, the recruiter will describe the study in detail and bring the eligible participant through the information and consent form. If the eligible participant agrees to join the study she will be asked to sign the consent form. The same process will be used for all 3 groups (high treatment, low treatment, and comparison).

**10.2 Blinding**

Researchers assessing the study outcomes will be blinded to the randomised allocation. Participants (i.e. parents) will be informed of their randomised allocation.

**10.3 Randomisation**

Participants will be randomised after informed consent is obtained using an unconditional probability randomisation procedure. No stratification of block techniques will be used. A computerised programme will be used to create an array of numbers populated with a one or zero equal to the required sample size. This array will be shuffled using a random number generator to randomly assign the numbers a location in the array. To ensure randomisation is not compromised the participant will press a key on a computer which randomly allocated her treatment group assignment. Once assignment is completed, an automatic email will be generated which includes the participant’s unique ID number and assignment condition. This email will be automatically sent to the *PFL* programme manager and the evaluation manager. This method will be used to ensure that the recruiter has no influence on the treatment assignment. Thus, if any attempts to reassign participants from one group to another group, by either directly changing the database or repeating the randomisation procedure, a second email will be generated to automatically highlight this intentional subversion.

# 10.4 Assessments

**Timing:** Data will be collected from both the programme participants (both high and low treatment groups) and the external comparison group within the same time period. Baseline data will be collected after confirmation of informed consent/randomisation assignment and before the programme begins. Subsequently, data will be collected when the infants are 6, 12, 18, 24 months of age and then each subsequent year (36 & 48 months) until the study child starts school (at age 4/5). Records from the maternity hospitals will be collected after the birth of the child and records from the children’s hospital will be collected when the child is at least 4 years old. It is important to collect data more regularly during the early stages of the child’s development as the evidence based on US interventions e.g. the Early Head Start programme, found that interventions have the greatest impact between 12 and 18 months. In addition, more data points will help track developmental trajectories. In total, eight waves of data will be collected. As the data collection will be sequential, each family will be interviewed when the child is the same age.

**Informant*:*** A combination of data capture methods will be used to produce optimum quality data. The primary informant at household level will be the mother through CAPI interview. The father, if available and living in the household, will also be required to participate in a shorter self-administered interview. Based on a scoping survey we estimate that about 50% of children will have biological parents living apart. If contact details are available from the mother, the absent biological father will be contacted and asked to complete the self-administered questionnaire. Data will also be collected on any siblings in the household. These data are crucial for evaluation of the RCT component, as given the design of the programme a pre-test (i.e. a pre-test measures outcomes prior to service delivery to facilitate comparison with post programme outcomes), is not possible. Therefore examining the key outcomes of the siblings of the PFL children before the programme begins will allow us to determine whether the parents’ behaviour, and its subsequent effect on the PFL children, differs before and after PFL. Additionally, data will be collected from junior infant school teachers (using the early development Instrument).

**Interviewers*:*** All interviews will be conducted by trained research assistants. The researchers will receive specialised training from our training partners, the National Centre for Social Research (NatCEN), to minimise interview bias. Specialised training will be required for this study as it involves working with children and parents on sensitive issues and standardising measurements of height and weight to minimise inter and intra-observer variation.

**Assessments & Contact Time*:*** Appointments to schedule the data collection and assessment interviews will be made in advance by telephone and will be considerate of the respondents’ needs and availability. Family contact time for data collection will be confined to about 2 hours per case, with a natural break in between. The 2 hours duration for data collection has been widely established in other studies as the optimal duration for maximizing the amount of data collected and minimizing participant fatigue and attrition from the study. Allowing sufficient time is necessary as it is important for families to feel that they are being carefully listened to by the interviewers if the goal is to assess their current life situation, their needs, and their perceptions about PFL services they are receiving.

**Computer-Aided Personal Interviews *(CAPI):*** Data collection will be achieved using Computer-Aided Personal Interviews (CAPI) in the home setting. Using this method, data entry, editing, and verification procedures are programmed into a laptop computer. The interviewer – or the respondent – records answers to each question using the keyboard or screen. Automatic routing ensures that there are no interviewer-driven errors in asking the correct question. One advantage of the home setting is that it provides access to fathers who appear to be more willing to participate if data collection occurs conveniently in the home. Another advantage of the home setting is that measures of parenting skills and the home environment can be obtained. This is particularly useful since the intervention focuses on parenting practices.

**Self-completed Interviews*:*** At the time of the interview with the principal informant in the household (usually the mother), it is planned to give all fathers present a self-completion questionnaire. The data will be entered onto a computer as rapidly as possible after completion. In addition, as the children advance in age, interviews will be conducted with them, so as to ensure that the voice and mind of the child is captured in as an informative but unobtrusive a way as possible.

Justification of Assessments*:* In order to be ready for school, children need to have attained several physical, cognitive and social developmental milestones. There are numerous factors determining a child’s level of school readiness, but the risks are correlated and tend to be concentrated in low socioeconomic status families. Maternal education, educational quality of the home environment, and socioeconomic status (SES) appear to be the best predictors of children’s early grade school success (Horvat & Svetina, 1993; Ricciuti, 1999; Ketterlinus, Henderson, Lamb, 1991; Kinard & Reinherz, 1987). Children from very low SES backgrounds are more likely than other children to exhibit deficits in their verbal abilities, visual-motor abilities, and motor abilities (Costeff & Kulikowski, 1996). Such risks, which many of the PFL children may face, begin to act as early as the prenatal life period, with maternal health behaviors during pregnancy. Mothers who live in economically deprived conditions are more likely to experience stress and to consume alcohol and nicotine during pregnancy. In the post-natal period, parental behaviours and attitudes, such as expectations and parenting practices in early childhood, as well as the effective bond between parents and their children, have been found to predict early grade school success. In addition, disadvantaged children tend to experience lower quality of education in the home (e.g. lower number of books, less frequent reading by parents) which is predictive of school readiness (Clarke and Kurtz-Costes (1997). Importantly, crèche and preschool experiences can enhance the cognitive development of low-SES children (Geoffroy et al., 2007). Thus, school readiness and early academic achievement are determined by a number of children’s characteristics and environmental influences that come together during first few years of life. Consequently, assessment of the impact of the PFL intervention and of the mechanism of action will carefully examine the social, physical and cognitive development of the child, his/her family background, home environment, and preschool environment.

Survey Instruments*:* Table 1 below lists the complete set of instruments which will be collected over the 8 data assessment point. The assessments will be divided into two part – the primary child outcome measures and the secondary parent outcome measures. The parent information will include 1) Demographic/Household, 2) Employment/Income, 3) Pregnancy, 4) Parenting/Neglect, 5) Maternal Social Support, 6) Maternal Socio-emotional Functioning, 7) Maternal Health, 8) Maternal Drug/Alcohol Use, 9) the Home Environment, 10) Breastfeeding, 11) Childcare Decisions, 12) Maternal Cognitive Assessment, 13) General Questions, 14) Programme Satisfaction, 15) Open-ended Questions, 16) Sibling Behaviour. The child information will include 1) Child Development and 2) Child Health. The specific instruments for each domain are listed in Table 1.

Providing Feedback to Families after Assessment*:* The interviewer will end each interview sessions with a debriefing in which the interviewer will thank the respondents for their time and ask them if they have any questions and how they felt the interview went. If an assessment reveals that a child is above a certain level of clinical risk, in terms of developmental delay for example, we will inform the parents of this and write a letter referring them to the appropriate agency. It should be noted that this may bias the results of the impact evaluation if a significant number of children are at this level, however it is essential to maintain a balance between scientific rigor and ethical considerations.

**Maintaining Contact with Families Between Assessments*:*** The research team will maintain contact with the PFL families and the external comparison group between assessments using the Database Management System (DBMS) to enable contact with, and tracking of, participants. This system will be used to track the consent status and any contacts between the researchers and the PFL participants, as well as change of address or any other factors that may affect the researcher’s ability to carry out the evaluation. A lo-call number will also be maintained in order for families to contact the research team. In addition, a programme newsletter which talks about the importance of evaluating the programme and highlights some basic data findings may help the participant families to better connect with the research side of the programme.

[figure not shown]

[figure not shown]

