**5.2 Secondary endpoints**

1. **Birth outcomes:** maternity hospital records at birth (birth weight, gestational age, prematurity, Apgar score).
2. **Labour outcomes:** maternity hospital records at birth (instrumental delivery, caesarean section- elective, emergency).
3. **Parenting skills:** Adult Adolescence Parenting Inventory (at baseline &12 months); Knowledge of Infant Development (at baseline & 12 months); Parental locus of control (at 6 months); Condon Maternal Attachment Scale (at 6 & 24 months); Parenting Stress Index (at 6, 24 & 48 months); Parenting Daily Hassles Scale (at 18, 36 & 48 months).; Maternal Separation Anxiety (at 18 months); Parental Cognitions and Conduct Towards Infant Scale (at 6 & 24 months); Parenting Styles and Dimensions Questionnaire (at 36 & 48 months); Parental Acceptance -Rejection Questionnaire (at 36 months).
4. **Quality of the home environment:** Home Observation for Measurement of the Environment scale (at 6, 18 & 36 months); Activities with child (at 6, 18, 36 months); Home Learning Environment (at 48 months); Material Deprivation scale (at 18 months); Framingham Safety Survey (at 6, 18, & 48 months); Family Environment Scale (at 12 &36 months); Difficult Life Circumstances (18 & 36 months); Neighbourhood Quality Evaluation Scale (at 36 months); Family Routine Inventory (at 36 months).
5. **Parent health:** physical health outcomes (self-reported) (at baseline, 6, 12, 18, 24, 36, 48 months); personality (Tem-Item Personality Inventory (baseline), Rosenberg self-esteem (at baseline12, 18, 48 months) Pearlin Self-Efficacy Scale (at baseline,12 & 48 months) ; Vulnerable Attachment Style Questionnaire (baseline); Considerations of Future Consequences (at baseline & 24 months); Future Outlook Inventory (at 12, 36 months); Self-control (at 18 months); mental health outcomes (Edinburgh Postnatal Depression Scale at 6, 18, 24, 36, & 48); WHO-5 Index (at baseline, 6, 12, 36, 48).
6. **Social support and service use:** Level from support from various people (at 6, 18, 24, 36, & 48 months); community integration (at 6, 12, 18, 24, 36, 48 months); use of services (at 6, 18, 36 months); partner satisfaction (at 6, 12, 24, 48 months); Maternal Social Support Index ( at 18 & 36 month); Family Quality of Life (at 36 months); Relationship Quality Index (at 36 months).

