| **Cognitive Assessment** | Maternal Intelligence: *Wechsler Abbreviated Scale of Intelligence (WASI)* |  | X |  |  |  |  |  |  |
| **General Questions** | Voting Behaviour | X |  | X | X | X | X | X | X |
| Breathing Vignettes |  |  | X |  |  |  |  |  |
| Age Related Questions |  |  |  | X | X | X | X | X |
| Relevant Notes About Interview |  |  | X | X | X | X | X | X |
| **Programme Questions** | Client Satisfaction with Programme |  |  | X | X |  | X | X |  |
| Frequency Mentor/IO Meetings |  |  | X | X | X | X | X | X |
| Contamination Questions |  |  | X | X | X | X | X | X |
| **Hopes/**  **Dreams/**  **Strengths/**  **Difficulties** | Mother’s Hopes and Dreams for New Baby | X |  |  |  |  |  |  |  |
| Family Problems that may Affect New Baby (Mother’s View) | X |  |  |  |  |  |  |  |
| Family Strengths and Qualities (Mother’s View) | X |  |  |  |  | X |  | X |
| Thoughts on being a Mam |  |  | X |  |  | X |  | X |
| Important Events Since Last Interview (Mother’s View) |  |  | X |  | X |  | X | X |
| **Sibling Behaviour** | Sibling Behaviour Questions (for 4 year old siblings only): *Newly Designed Instrument* |  |  | X |  | X |  |  |  |

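### The sibling data meant to stand in for a pre-test are first scheduled at 6 months, and the baseline interview follows allocation, so neither is secured as a pre-allocation measure

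*Protocol*

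**What the plan says.** On the sibling data, Protocol section 10.4 (Informant) explains that a pre-test is impossible under this design and treats sibling data as crucial for evaluating the randomised component. The plan depends on "examining the key outcomes of the siblings of the PFL children before the programme begins", so as to judge whether parental behaviour differs before and after PFL. Table 1, which section 10.4 presents as the complete instrument list, has one sibling row: "Sibling Behaviour Questions (for 4 year old siblings only"), marked at 6 and 18 months. Section 7.1 has the programme start during pregnancy.

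On the order of baseline and allocation, section 10.3 states "Participants will be randomised after informed consent is obtained" and that "the participant will press a key on a computer which randomly allocated her treatment group assignment". Section 10.2 adds: "Participants (i.e. parents) will be informed of their randomised allocation". Section 10.4 (Timing) then says: "Baseline data will be collected after confirmation of informed consent/randomisation assignment and before the programme begins". On who supplies the data, the same section says: "The primary informant at household level will be the mother through CAPI interview".

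Section 5.2 lists several maternal self-report endpoints with a baseline value, for example "Adult Adolescence Parenting Inventory (at baseline &12 months"). Section 12.2 (Differential Attrition) uses baseline characteristics as predictors in the logistic models behind the inverse probability weights.

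**The concern.** Both measures are meant to describe the family before the programme could have any influence, and the protocol secures neither.

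The sibling measure is the protocol's own substitute for a missing pre-test. If its first observation comes after months of home visiting, there is no before value, and the comparison that justifies collecting it is lost. This is a data-collection schedule, so a later analysis plan cannot restore what was never measured.

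The baseline interview still precedes programme content, so only knowledge of the assigned group can affect it. Much of it asks a mother about her parenting attitudes, well-being, self-esteem and support, and such answers can move with hope or disappointment about the group drawn. At stake are the baseline values of several secondary endpoints, any analysis that uses them, and the attrition weights. There is also a window between key press and interview in which a randomised woman can be lost without leaving any baseline data.

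**Working it through.** The protocol states no figure on this point, so there is none to reproduce. The check sets the passages side by side, with one small count.

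**Sibling schedule**

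1. Table 1 columns run BL, 3, 6, 12, 18, 24, 36, 48. The sibling row is blank under BL and 3, marked under 6, blank under 12, marked under 18 and blank thereafter.
2. The programme starts in pregnancy (section 7.1), with two home visits a month in the high treatment group. The low treatment group also receives developmental materials, book packs and access to a support worker (section 7.2).
3. Planned visits since birth = 2 per month × months of age. At 6 months this is 2 × 6 = 12; at 18 months, 2 × 18 = 36. Prenatal visits are extra.
4. Pre-programme sibling observations: 0 of the 2 scheduled.
5. Baseline items that touch on earlier children, such as breastfeeding or postnatal depression in previous pregnancies, describe the mother's history. They are not sibling outcomes and do not fill the gap.

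**Order of baseline and allocation**

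1. Section 10.3 gives consent, then the key press. Section 10.4 places baseline after consent/randomisation assignment. The slash reads most naturally as consent for the external comparison group, which is not randomised, and assignment for the two randomised groups.
2. Section 10.2 says parents are told their group. The moment is not stated, and nothing delays disclosure until after baseline. That the mother knows her group at the interview is therefore an inference, though the natural one.
3. Secondary endpoints in section 5.2 that are self-reported by the mother and have both a baseline and a later value include the AAPI, KIDI, Rosenberg self-esteem, Pearlin self-efficacy, WHO-5 and Consideration of Future Consequences. A shift between arms at baseline would enter any adjusted, change or moderator analysis of these.
4. The weights in section 12.2 are predicted from baseline characteristics and applied in both the regressions and the permutation tests. Two consequences follow:
   - Predictors that allocation can alter may carry the effect of knowing one's group into the weights.
   - A woman lost between key press and interview has no predictor values and cannot enter the weighting model.
5. The tests of child outcomes in section 12.2 compare group means, with no baseline covariate adjustment stated. The timing of baseline does not enter an unadjusted comparison of that kind.

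**The case against.** The strongest reply is that neither issue touches a stated primary analysis. Child school readiness has no baseline, because the children are unborn, and section 12.2 prescribes no covariate adjustment and no sibling estimator. This stands, and it limits the point to the weighted estimates, the secondary endpoints with a baseline value, moderator analyses and the sibling comparison.

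Much of the baseline also cannot plausibly be changed by learning one's group: age, ethnicity, education, pregnancy history. Predictor choice for the weights may properly be left to an analysis plan. This too stands, and it supplies the remedy if enrolment has already happened. It does not help women with no baseline record.

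Loss on learning the group is hypothetical: eligibility requires willingness to join either group, and consent stresses random allocation. That is fair, and no count is claimed here.

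On siblings, a child aged 4 at the 6-month wave was at least 48 − 6 = 42 months old when the study child was born, so most of that child's life preceded the programme. The 6-month measure is thus less exposed than the 18-month one. It is still not the pre-programme measure that section 10.4 describes, since the parents have been in the programme since pregnancy.

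A reader might infer more than the documents support:

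- That the intention-to-treat contrast is biased beyond repair. The unadjusted comparison is unaffected by when baseline is measured, and weighting or adjustment can be confined to unalterable items.
- That the bias can be expressed in standard deviations. The protocol gives neither a size for the shift nor a baseline–outcome relation, and the bias of a weighted estimate is not the product of the two.
- That spill-over to siblings would be deducted from the programme effect. No analysis in section 12.2 subtracts sibling outcomes.

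**Conclusion.** The sibling point is a contradiction within the protocol and needs no assumption. Section 10.4 relies on sibling outcomes from ahead of the programme, while Table 1 provides none, the first falling about 12 planned postnatal visits into the high treatment programme. As scheduled, the before/after comparison cannot be made.

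The ordering point is an avoidable weakness, and its consequences are limited. That baseline follows assignment is stated; that the mother knows her group by then is inferred. On that inference, self-report baseline values of secondary endpoints, analyses using them, and weights built on alterable items are open to distortion of unknown size. The gap in the weighting model for women lost before the interview follows from the ordering alone, whatever the mother knows. The unadjusted intention-to-treat comparison of child outcomes is not affected by the timing of baseline. The change is worth making; nothing here shows the main comparison to be invalid.

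**What to change.** - In sections 10.3 and 10.4, set the order as consent, completed baseline interview, then key press and disclosure of the group.
- If enrolment has already taken place, restrict weighting and adjustment variables to items that allocation cannot alter, such as maternal age, parity and education. Report losses between allocation and baseline by arm.
- In Table 1, add the sibling questionnaire at baseline, using the same instrument. Otherwise, withdraw from section 10.4 the claim of a sibling comparison from ahead of the programme.

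The cost is small. Reordering adds no step, because baseline already precedes the programme. The sibling addition makes the baseline interview slightly longer for families with a 4-year-old. Withdrawing the claim costs only the comparison, which the present schedule cannot deliver anyway.
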